### Sample selection

The study sample will comprise individuals with no history of cardiovascular disease (except for SAH controlled with the use of medications), neuromuscular, endocrine, and/or metabolic conditions (except for diabetes mellitus type 2) who are attending the IC health care facilities.

Subjects will be selected based on information collected from their medical records. Eligible individuals will be contacted by telephone and informed of the purpose and procedures of the study. For those willing to participate, a first visit will be scheduled when a clinical questionnaire will be administered, and they will be asked to sign a free informed consent form to participate in the study. Other study visits will be scheduled for those meeting the inclusion criteria of the study (Table 3).

**Table 3 Tab3:** Inclusion and exclusion criteria for the study

Inclusion criteria	Exclusion criteria
• Males and females aged 18 to 70 years • Diagnosed with SAH • Signed a free informed consent form • Considered insufficiently active (IPAQ) • Non-active smokers	• Currently engaging in any type of systematic physical activity • Blood pressure hyper-reactivity in the clinical assessment (SBP > 220 mmHg and/or increase in DBP > 15 mmHg) • Ongoing infectious diseases • Obesity class II or III (BMI) • Heart failure class III or IV; recent cardiovascular event (in the last three months); chronic renal failure; and malignant disease with life expectancy < 2 years • Orthopedic impairments or any physical or mental limitations that prevent physical exercises • After the training intervention, individuals who attended < 85 % or missed > 2 consecutive training sessions will be excluded from the sample. Subjects will be encouraged to complete any missed session at the end of training by performing additional sessions.

SAH, systemic arterial hypertension; IPAQ, International Physical Activity Questionnaire; SBP, systolic blood pressure; DBP, diastolic blood pressure; BMI, body mass index

The following formula will be used for the calculation of sample size (n_p_) to estimate the number of hypertensive individuals to be included in the study:$$ \left({\upmu}_{\mathrm{p}}\right):\ {\mathrm{n}}_{\mathrm{p}0} = {\mathrm{s}}^2/\ {\left({\upmu}_{\mathrm{p}}\hbox{-}\ {\mathrm{x}}_{\mathrm{p}}\right)}^2\mathrm{x}\ {\left({\mathrm{t}}_{\upalpha; \mathrm{g}\mathrm{l}}\right)}^2, $$

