where, n_po_ = sample size at time point zero, s^2^ = variance of the sampling distribution, and t_α;gl_ = sampling distribution according to a predetermined error probability (*P* ≤ 0.05) and degrees of freedom for n_po_.

The mean incidence rate of SAH in Brazil is 20 % of the population [40]. Considering the baseline value (n_0_ = 30); t_α;gl_ = t_0.05;29_ = 2.045; s^2^ = 0.05 (based on the maximum value of the coefficient of variation of endothelial vasodilation); and the maximum error of the estimate taken as the maximum variability in arterial diameter measures by two observers (0.02 %) [41], it was estimated that n_p1_ = 26.1 ≅ 26 hypertensive individuals. Thus, in the estimate of *n,* the approximation used considered n_p1_ = 26, gl = 23, and t_0.05;23_ = 2.069. The n_p1_ = 26.8 ≅ 27. The estimate of the sample size for the study was *n* = 80.3 ≅ 81 hypertensive individuals who will be randomly assigned to the three training interventions.

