### Randomization procedure

A randomization for the proposed interventions will be generated by a computer program (www.randomization.org) including the distribution coded at a 1:1 ratio. The random assignment of subjects to training intervention groups will be into three blocks of 27. Subjects will be drawn up to 27 in each intervention group: aerobic training (AT), resistance training (RT), and combined training (CT, resistance and aerobic). All subjects will be blinded to intervention allocation and will have access to this information only after the baseline assessment. All evaluators of the study subjects will be also blinded to intervention allocation.

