### Assessment of flow-mediated dilation (FMD)

Endothelial function will be measured noninvasively by using brachial artery ultrasound (EnVisor series, Philips Ultrasound, Bothell, WA, USA). This assessment will be performed with a 7 to 12 MHz linear transducer in a heated room at 21 to 24 °C at ICFUC. A software program will be used for two-dimensional color-Doppler imaging acquisition with a simultaneously recorded electrocardiogram (ECG). Image data will be recorded on a DVD. To minimize operational errors, the subject’s arm, and the ultrasound transducer will be positioned and maintained in the same position during the procedure. Baseline images will be recorded. A cuff will be placed around the forearm and inflated to 50 mmHg above systolic pressure for at least 5 min and then removed. Longitudinal ultrasound images of the brachial artery walls will be acquired to assess endothelium-dependent vasodilation. The expected coefficient of variation between the images will be 1.8 to 5.0 %. Flow-dependent vasodilation responses will be expressed as the percentage change in the brachial diameter [36].

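### The calculated 27 per arm is also the most that each arm can take in, so one exclusion after training puts that arm below the stated size

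*Protocol article*

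**What the plan says.** All statements are in the protocol article.

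- **Sample selection, sample size.** A one-sample precision formula (variance over squared error, times squared t) is started with "Considering the baseline value (n_0_ = 30); t_α;gl_ = t_0.05;29_ = 2.045" and repeated once: "the approximation used considered n_p1_ = 26, gl = 23, and t_0.05;23_ = 2.069". This gives 26.8, rounded to 27. The total follows: "The estimate of the sample size for the study was *n* = 80.3 ≅ 81 hypertensive individuals who will be randomly assigned to the three training interventions", that is, three arms of 27.
- **Randomization procedure.** "Subjects will be drawn up to 27 in each intervention group".
- **Sample selection, Table 3.** After training, "individuals who attended < 85 % or missed > 2 consecutive training sessions will be excluded from the sample". The same entry encourages subjects to make up missed sessions at the end of training.
- **Intervention protocols.** Three sessions a week for 12 weeks. Subjects with repeated high blood pressure go to the study cardiologist, who decides whether they continue, so there is a second route out.

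No loss rate is given, no allowance for loss is added between the formula and the total, and replacement of excluded subjects is not mentioned.

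**The concern.** The calculated requirement equals the number randomised, the number randomised is a ceiling, and the protocol then plans to take subjects out. Nothing in the sequence puts any back. So the 27 per arm is a starting number, while the error target it was calculated for applies to the number that remains in the estimate.

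At stake is how the stated precision is read. If an arm ends with 26 or fewer, the article's own criterion is no longer met in that arm, and nothing in the sample size paragraph warns of this. The point is separate from whether a one-sample precision formula suits a three-arm comparison, and from the bias that attendance-based exclusion can cause. It holds for whatever requirement is accepted.

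**Working it through.** **1. Reproducing the stated size.** Formula in the article: n = s² / error² × t².

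The printed inputs are "s^2^ = 0.05 (based on the maximum value of the coefficient of variation of endothelial vasodilation" and an error described as "maximum variability in arterial diameter measures by two observers (0.02" per cent. The FMD section says "The expected coefficient of variation between the images will be 1.8 to 5.0" per cent, which suggests that 0.05 is a coefficient of variation, that is, an SD and not a variance.

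| Reading | t = 2.045 | t = 2.069 | × 3 arms |
|---|---|---|---|
| s = 0.05 (s² = 0.0025), error 0.02 | 26.14 | 26.75 | 80.26 |
| s² = 0.05 as printed, error 0.02 | 523 | 535 | 1605 |

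Only the first row gives the article's 26.8 and 80.3. Reading the error as 0.02 % (0.0002) gives at least 261,000 per arm. The rest of the check uses SD 0.05 and error 0.02, inferred from the printed n.

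The second t value uses 23 degrees of freedom for n = 26. With 25 degrees of freedom (t = 2.0595) the result is 26.5, still 27.

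**2. Slack.** 27 − 26.75 = 0.25 subject per arm.

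**3. Effect of losing subjects.** Half-width = t(0.975; n − 1) × 0.05 / √n.

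| n in the arm | Half-width | Target 0.02 |
|---|---|---|
| 27 | 0.0198 | met |
| 26 | 0.0202 | missed |
| 25 | 0.0206 | missed |
| 24 | 0.0211 | missed |
| 23 | 0.0216 | missed |

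**4. Number left under an assumed loss.** The loss rates are assumptions.

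| Loss | Per arm, 27 × (1 − loss) | Half-width | Chance that none of 81 is lost, (1 − loss)^81 |
|---|---|---|---|
| 5 % | 25.7 | 0.0203 | 1.6 % |
| 10 % | 24.3 | 0.0210 | 0.02 % |
| 15 % | 23.0 | 0.0216 | below 0.01 % |

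The last column assumes independent losses.

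**5. What the attendance rule alone could remove.** 12 × 3 = 36 sessions and 0.85 × 36 = 30.6, so 31 must be attended. A subject is excluded with 6 or more missed, or 3 or more missed in a row. Simulated with each session attended independently (an assumption), at the two extremes for make-up sessions:

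| Mean attendance | No make-up: excluded (left per arm) | Full make-up, only runs of 3 exclude: excluded (left per arm) |
|---|---|---|
| 95 % | 1.1 % (26.7) | 0.4 % (26.9) |
| 92 % | 7.3 % (25.0) | 1.6 % (26.6) |
| 90 % | 15.7 % (22.8) | 3.0 % (26.2) |
| 88 % | 27.1 % (19.7) | 5.1 % (25.6) |

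In the favourable column the chance of at least one exclusion among 81 is 1 − 0.996^81 = 0.28 at 95 % attendance, 1 − 0.984^81 = 0.73 at 92 % and 1 − 0.970^81 = 0.92 at 90 %. Neither column includes ordinary dropout or clustered absences, both of which add losses.

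**The case against.** The best case for the protocol is that the loss may be very small. Make-up sessions stand in the same table entry as the exclusion, and if they restore the attendance count, exclusions stay between 0.4 and 5.1 % over the attendance range above. This stands as a limit on size. It does not remove the point: the text does not say that a make-up session cancels a run of more than two missed sessions, and one exclusion is enough to miss the target.

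Replacement is neither allowed nor forbidden, the article is condensed and the flow chart is not shown. That also stands, so the claim is only that none is described. The calculation itself is printed from formula to total, and no allowance enters it.

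Four stronger readings are tempting but not supported:

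- *The analysed sample is bound to be well below 27.* The documents give no attendance or loss figure, and falling below 27 requires at least one loss in an arm.
- *The trial loses power.* The article states no power and no between-arm difference, so any power figure would rest on an invented effect size.
- *A half-width of 0.0216 follows from the article's inputs.* With s² = 0.05 as printed (SD 0.2236), it is about 0.088 at n = 27 and 0.097 at n = 23, so a 0.02 target is missed before any loss.
- *The article passes off 81 as the number analysed.* It says that the 81 will be randomised. What it leaves unsaid is that fewer may remain in the estimate.

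**Conclusion.** The point holds in a limited form. Three explicit statements (27 required, at most 27 taken in, exclusion after training) do not fit together unless no arm loses a subject. It is an inconsistency between sections, and the multiplication itself is sound on the inputs that reproduce it.

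The size is modest. One exclusion moves the half-width from 0.0198 to 0.0202, and a 15 % loss moves it to 0.0216, about 9 % wider (0.0216 / 0.0198 = 1.09). These figures rest on SD 0.05 and error 0.02, inferred from the printed n, and on assumed loss rates. The conflict between the sections depends on neither. It is worth correcting because the correction is cheap, but it is not a serious fault of the design.

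**What to change.** In the sample size paragraph of Sample selection:

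1. State that 27 per arm is both the calculated requirement and the number randomised, and that the number analysed will be lower once anyone is excluded under Table 3.
2. Give the expected number analysed per arm over a loss range labelled as assumed, for example 25.7 at 5 %, 24.3 at 10 % and 23.0 at 15 %. Add that make-up sessions lower the loss and that dropout or clustered absences raise it.
3. Correct the printed variance and error first, then restate the precision for those numbers. If SD 0.05 and error 0.02 are confirmed, the half-widths are 0.0198 at 27, 0.0202 at 26 and 0.0216 at 23.
4. Add no power statement on this basis.

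The cost is a few sentences and a slightly less favourable stated precision. No extra subjects or procedures are needed.

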### Randomization procedure

A randomization for the proposed interventions will be generated by a computer program (www.randomization.org) including the distribution coded at a 1:1 ratio. The random assignment of subjects to training intervention groups will be into three blocks of 27. Subjects will be drawn up to 27 in each intervention group: aerobic training (AT), resistance training (RT), and combined training (CT, resistance and aerobic). All subjects will be blinded to intervention allocation and will have access to this information only after the baseline assessment. All evaluators of the study subjects will be also blinded to intervention allocation.

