## Background

Cardiovascular diseases are largely determined by multifactorial risk factors that tend to interact and may be present over the course of an individual’s lifetime. Obesity [1, 2], physical inactivity [3, 4], and insulin resistance [5] are all risk factors closely associated with systemic arterial hypertension (SAH) and diabetes mellitus type 2. In addition to these risk factors, smoking [6] and excess weight [7] contribute to endothelial dysfunction [8, 9], which is a hallmark of diabetes mellitus [10] and SAH [11] and an early maker for atherosclerosis [12].

The endothelium is a single layer of cells that lines the tunica intima of blood vessels [13] and plays a major role in the modulation of vascular angiogenesis, inflammatory responses, and vascular tone and permeability [14]. Vascular protection is particularly attributable to endothelial nitric oxide synthase (eNOS), an enzyme involved in the production of nitric oxide (NO).

The balance between endothelial injury and recovery is critical to continuously maintaining endothelial function [15]. The bone marrow releases a progenitor cell subtype called endothelial progenitor cells (EPCs), which have the ability to migrate to the peripheral circulation and differentiate into mature endothelial cells to maintain vascular integrity [16]. EPC levels have been associated with cardiovascular risk factors [17], endothelium-dependent vasodilation [18], and clinical outcomes, including hospitalization and cardiovascular death rates [19]. In patients with cardiovascular risk factors such as SAH [20], smoking [21], metabolic syndrome [22] and diabetes mellitus [23], circulating levels of EPCs can be reduced compared with healthy individuals of matching age and sex. Endothelial dysfunction has been associated with a decreased number and impaired function of EPCs in patients with SAH, diabetes mellitus, and metabolic syndrome, and thus an increased risk of atherosclerosis would be expected [24].

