A basic training principle is the progression of exercise intensity, duration, or frequency. Progression of exercise in the study intervention will be through gradual exertion increase for the protocols [46]. Borg’s rating scale of perceived exertion (6 to 20 point scale) will be used to help control the training intensities [47]. All subjects will be allowed an initial adjustment period. Those with resting BP levels higher than 160 mmHg (SBP) and/or 105 mmHg (DBP) before cardiopulmonary testing, 1-RM, or an exercise session (AT, RT and CT) will not be allowed to participate in any activities [40]. Those experiencing BP higher than the recommended level on a second occasion will be referred to the study cardiologist for evaluation. The cardiologist will determine whether the subject can continue participating in the study.

Subjects diagnosed with SAH and diabetes mellitus type 2 will have their blood glucose checked (Optium Xceed, Abbott Diabetes Care, Inc., Alameda, CA, USA) in addition to BP measurements before cardiopulmonary exercise testing, 1-RM or an exercise session (AT, RT, and CT) and every 15 min throughout exercise sessions. If the blood glucose levels are lower than 100 mg/dL during cardiopulmonary exercise testing, 1-RM, or exercise sessions (AT, RT and CT), subjects will receive 30 to 45 g glucose gel (Gli-Instan, Lightsweet ™) to maintain levels above 120 mg/dL, and their blood glucose will be checked again 15 min later. Those with blood glucose higher than 250 mg/dL will have their urine tested for the presence of ketones (ComboStik™, Gyung-Nam, Korea), and they will be allowed to resume exercise only if test results are negative. Subjects with blood glucose lower than 100 mg/dL during exercise sessions will have to discontinue exercising and be offered a snack. Their blood glucose will be tested again 15 min later, and they will be allowed to resume exercise only if their test results are acceptable [48].

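### Type 2 diabetes, which the protocol links to FMD and EPC counts, is neither a stratification factor nor a named adjustment factor: a modest loss of precision and robustness, not bias

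*Protocol article*

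**What the plan says.** - **Eligibility.** Under Sample selection, other endocrine and metabolic conditions are ruled out, but type 2 diabetes is let in: "endocrine, and/or metabolic conditions (except for diabetes mellitus type 2". No cap and no expected share is given.
- **Allocation.** Under Randomization procedure: "The random assignment of subjects to training intervention groups will be into three blocks of 27", and "Subjects will be drawn up to 27 in each intervention group". No stratification factor is named.
- **Diabetes and the outcomes.** The Background says of endothelial dysfunction: "which is a hallmark of diabetes mellitus [10] and SAH [11". For patients with SAH, smoking, metabolic syndrome or diabetes it says that "circulating levels of EPCs can be reduced compared with healthy individuals of matching age and sex", and it adds: "Endothelial dysfunction has been associated with a decreased number and impaired function of EPCs in patients with SAH, diabetes mellitus, and metabolic syndrome". FMD and EPC count are both primary objectives in Table 1. So is the endothelial microparticle count, which the text does not tie to diabetes.
- **Diabetes status is known early.** Under Intervention protocols, diabetic subjects have their glucose checked before the cardiopulmonary test, before 1-RM testing and around each session.
- **Analysis.** Statistical procedures lists multivariate linear regression among the candidate methods and names no covariates.

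**The concern.** All subjects have SAH, so SAH cannot differ between arms. Diabetes can, and the protocol's own Background presents it as related to two of the primary outcomes. With 27 per arm, simple chance can leave the arms visibly different in diabetic share.

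Two things are at stake:

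- **Precision.** An outcome predictor left out of both the allocation and the model stays in the residual variance and lowers power.
- **Robustness.** In those trials where the arms happen to differ, the unadjusted comparison is less trustworthy than its nominal 5% level suggests, and a reader of the results will ask about it.

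**Working it through.** **The plan's own figure.** With 0.05 as the spread, 0.02 as the error and t = 2.069, the sample size formula gives (0.05/0.02)² × 2.069² = 6.25 × 4.281 = 26.75 per arm. Three times that is 80.26, rounded up to 81, so 27 per arm is reproduced. (This works only if 0.05 is read as an SD, although the text labels it a variance; that is a separate matter.) The formula is a precision formula. It gives no between-arm difference and no SD of the FMD change, so the effects below are in SD units.

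**Inputs that are assumptions.** The documents give neither of these:

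- a diabetic share of 20%, 30% or 40%, that is K = 16, 24 or 32 of 81;
- a difference g of 0.5 or 1.0 SD between diabetic and non-diabetic subjects in the outcome analysed, with the SD taken within diabetes groups.

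**Step 1: chance imbalance.** The probability that the arms receive a, b and c diabetic subjects (a + b + c = K) is C(27,a) × C(27,b) × C(27,c) / C(81,K). Summing exactly:

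| Diabetic subjects | Highest minus lowest arm ≥ 5 | ≥ 6 | One named pair ≥ 5 | ≥ 6 |
|---|---|---|---|---|
| 16 | 27% | 15% | 13% | 6% |
| 24 | 40% | 22% | 18% | 10% |
| 32 | 42% | 28% | 21% | 13% |

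At a 10% share (8 subjects), the figures for the highest against the lowest arm fall to 9% and 2%.

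**Step 2: what a gap does.** Five subjects are 5/27 = 18.5 points. The shift in that arm contrast is 0.185 × g, or 0.09 to 0.19 SD. For comparison, the pairwise difference detectable with 80% power is (1.96 + 0.84) × √(2/27) = 0.76 SD.

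**Step 3: error rate.** Simulated with normal outcomes, three arms of 27 and no true arm effect, the unadjusted ANOVA rejects in about 5% of trials overall. Among the trials with a gap of at least 7 subjects (7/27 = 26 points; 6% to 17% of trials), it rejects in roughly 4% to 7% for g = 0.5 and 10% to 11% for g = 1.0. With diabetes in the model, this conditional rate is about 4% to 6%.

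**Step 4: precision.** Leaving diabetes out multiplies the residual variance by about 1 + g² × p(1 − p). For p = 16/81 = 0.198, p(1 − p) = 0.158; for p = 32/81 = 0.395, it is 0.239. The factor is therefore 1.04 to 1.06 for g = 0.5 and 1.16 to 1.24 for g = 1.0. Simulated power of the overall test, with one arm shifted by 0.7 SD (assumption):

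| g | Unadjusted | Adjusted | Gain |
|---|---|---|---|
| 0 | 0.74–0.75 | about 0.74 | −0.5 points or slightly more |
| 0.5 | 0.72–0.73 | about 0.74 | 1 to 2 points |
| 1.0 | 0.64–0.68 | about 0.74 | 6 to 10 points |

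**The case against.** The strongest reply is that nothing here is invalid. Equal unstratified allocation is a sound design, the overall error rate stays at 5% (Step 3), and chance imbalance is already part of the sampling variance. That stands, and it rules out several stronger readings.

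- A reader might infer that the arm comparison is **biased**. It is not. The expected imbalance under randomisation is zero, so the shift in Step 2 is chance error.
- A reader might infer that a sizeable imbalance is **likely**, or that it **would be read as** a training effect. Every probability in Step 1 is below one half, and for a named pair none exceeds 21%. Even a 26-point gap with a 1.0 SD shift raises the false-positive rate only to about one in ten.
- A reader might infer from the glucose rules ("Subjects with blood glucose lower than 100 mg/dL during exercise sessions will have to discontinue exercising and be offered a snack") that diabetic subjects receive **a different intervention by arm**. The rules are written alike for AT, RT and CT. They differ by diabetes status only, and the text does not say how often sessions would be interrupted.
- A reader might extend the point to **all** primary outcomes. The text supports it for FMD and EPC only.

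It is also fair to say that the pre/post comparison removes part of a difference in starting level. What remains is mainly a difference in response to training, for which the protocol gives no figure. The real value of g could therefore lie at or below the low end of the range. Sex, age and BMI are possible factors too. Diabetes stands out because it is the exception written into eligibility and the Background itself ties it to the outcomes.

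Finally, an unseen analysis plan may name covariates. That limits the adjustment half of the point. It does not reach the allocation scheme, which the article sets out itself.

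**Conclusion.** The point holds as a modest one about precision and robustness. The protocol identifies a baseline factor related to two primary outcomes, knows it at entry, and uses it in neither the stated allocation nor any named model term. Under an assumed 20% to 40% diabetic share and a 0.5 to 1.0 SD shift, adjustment gains between about 1 and 10 points of power and removes the excess conditional error when the arms differ. If diabetes does not predict the outcome, adjustment costs about half a point of power. At a 10% diabetic share the issue is small. The size rests on both assumptions, on normally distributed outcomes and on an assumed 0.7 SD arm effect, none of which the documents supply. The validity of the trial is not in question.

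**What to change.** 1. **Statistical procedures.** State that the between-arm comparisons of FMD and EPC count include type 2 diabetes at entry (yes/no) as a fixed factor, alongside the baseline value of the outcome. This also covers subjects already allocated. If the analysis plan already says so, a cross-reference is enough.
2. **Randomization procedure.** The trial status is recruiting. Where the list for the remaining subjects can still be changed, stratify it by diabetes (yes/no) with permuted blocks in place of the single scheme of 27 per arm. If it cannot be changed, keep the list and rely on item 1.

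The cost is one degree of freedom in the model, a new list for the remaining subjects if item 2 is taken up, and final arm sizes that may differ by one or two. No new data are needed, since diabetes status already determines who has glucose monitoring.
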